#### Secondary analyses

We will assess if the changes in PTSD symptoms observed might be considered clinically significant or reliable. We will assess clinically significant change (a decrease of > = 10 points on the PCL-5) and reliable change (as decrease of > = 5 points on the PCL-5) between the baseline and 2-week and 4-week post-intervention. All analyses will be carried out on veterans and emergency service personnel combined.Subgroup analysis of primary outcomes by stratification factors will be conducted using mixed MANOVA (intervention vs waitlist) × repeated measures on all outcomes (baseline vs 4-week post-intervention) separately for each stratification factor.A mixed MANOVA with one between-group factor (intervention vs waitlist control) and repeated measures on secondary outcomes (loneliness, expressed anger, work and social adjustment)Within-participant analyses will be used to assess change from baseline to 6 months and 12 months for the intervention group only.A psychometric analysis of process measures will be conducted via factor analysis and reliability analysis. Path analyses will explore the relationship of process measures regarding the intervention experience to mood change assessed via the POMS questionnaire and psychophysiological data during the intervention and change in outcomes.See item e. above.A cost-benefit analysis will be used to analyse the cost of effectiveness and social return of investment of intervention based on the Greater Manchester Cost-Benefit Analysis model, which allows for comparisons with other treatment/projects based on government-approved values.

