### Objectives {7}

Primary outcome objectivesAssess mean changes in mental health outcome measures (e.g. PTSD, see item “Outcomes {12}” for a full list) from pre- to post-intervention between active and control groups (see item “Statistical methods for primary and secondary outcomes {20a}” for analysis details).Secondary outcome objectivesAssess proportion of participants achieving clinically significant change and reliable change between 2-week pre- and 4-week post-intervention PTSD scores.Conduct sub-group analyses to evaluate mean change in primary outcomes by stratification factors (military veteran vs. ESP, PTSD severity, gender).Assess mean change in social loneliness, work and social adjustment, and anger expression from pre- to post-intervention between active and control groups.Assess mean change in primary outcome measures from baseline to 6 months and 12 months for the active intervention group only.Assess mean change in process measures (e.g. mood, see item “Outcomes {12}” for a full list) and physiological data (heart rate variability and eye movement) from day 1 to day 2 of the NBI experience.Assess the relationship between intervention experiences and changes in process measures from day 1 to day 2 of the intervention and their relationship to change in outcomes.We will also explore the cost-effectiveness and social return of investment of the intervention.

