### Trial design {8}

A randomised waitlist-controlled superiority trial with an allocation ratio of 1:1 and a 4-week follow-up. The primary outcome will be assessed at 2-week and 4-week post-intervention and compared with the waitlist control group. The total follow-up period is 12 months (intervention group only).

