#### Secondary outcome measures

Use subheadings (or just numbers that correspond to the objectives) under this heading following the same order as in the introduction statement of objectives:Using scores on the PCL-5 [9], we will assess the proportion of participants achieving clinically significant change and reliable change between 2-week pre- and 4-week post-intervention in the following ways: clinically significant change equates to a decrease in PTSD score of greater than or equal to 10, and reliable change reflects a decrease in PTSD score of greater than or equal to 5.Sub-group analyses will be carried out to evaluate mean change in the primary outcome measures (described above) by stratification factors (military veterans vs emergency service personnel), PTSD severity (high vs low), and gender (male vs female).The following measures of loneliness and expressed anger were included in the developmental phase and will be assessed as follows: Loneliness will be assessed by the Short Version of the Social and Emotional Loneliness Scale for Adults (SELSA-S) [13]: 2 weeks prior and 2- and 4-week post-intervention. Expressed anger will be assessed by the State–Trait Anger Expression Inventory (STAXI) [14], which measures how frequently participants have expressed anger verbally or physically in the last month. This will be taken 2-week pre-intervention and 4-week post-intervention. The Work and Social Adjustment Scale (WSAS) [15] is a 5-item measure of impairment in general social functioning. This will be measured 2-week pre-intervention and at a 6-month and 12-month follow-up since it will not be sensitive to short-term change. Mean change from baseline will be assessed for each of these outcomes for active intervention and control groups.Follow-up measures at 6 and 12 months: It is not possible to include long-term follow-up measures in the RCT because the waitlist group will receive the intervention after the RCT 4-week data collection is completed. Instead, we will take measures of PTSD symptoms, anxiety, depression, wellbeing, loneliness, expressed anger, and social functioning, to provide pre- and post-data from the intervention fishing group only at 6 months and 12 months after their intervention. We will also measure changes in NHS (National Health Service) service use and employment at these times. In addition, to gauge the impact of the NBI on long-term behaviour and engagement with nature-based activities, we will follow-up on the participant exit strategy to assess how participants have engaged with angling or other nature-based activities since the intervention. Mean change from baseline to follow-up will be assessed.Mean changes in process measures (mood and physiological changes) will be assessed between the beginning of day 1 of the intervention to the end of day 2. We will evaluate mood using the brief Profile of Mood States (POMS) [16]. Our developmental phase has shown that these measures are sensitive to detect change between arrival and departure at the intervention. Following consultation in the development phase, we include objective physiological measures of psychological states: pulse heart rate and heart rate variability and assess hypervigilance using a mobile eye-tracking device to quantify saccadic behaviour.*Measures of the hypothesised active elements of the intervention*: We developed an item pool during the developmental phase. These measures will be taken prior to departure. Eight items from the Perceived Restorativeness Scale (PRS) [17] measure perceived experience of restoration from the environmental surroundings. Bespoke questions have been developed to evaluate self-efficacy, experience of fishing, and being in a group of veterans. Fourteen questions explore participants’ experience of fishing (e.g. “I found I could focus on the fishing”). Eleven questions explored participants’ experience of peer support over the weekend (e.g. “I felt the people around me understood”). These questions are answered by participants at the end of day 2 of the intervention. We will assess the relationship between intervention experiences and changes in process measures and any potential interaction with outcome measures over the course of the trial.The cost-effectiveness and social return of investment will be analysed based on the Greater Manchester Cost-Benefit Analysis Model [18]. This will allow for comparisons to be made with other treatments and studies using government-approved values.

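### The planned active-versus-waitlist comparison of WSAS cannot be made, because no control has a WSAS value after baseline in the randomised period

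*Protocol article*

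**What the plan says.** Three places in the protocol article promise a comparison of WSAS between arms:

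- Objectives {7}: "Assess mean change in social loneliness, work and social adjustment, and anger expression from pre- to post-intervention between active and control groups".
- Secondary outcome measures, directly after the WSAS schedule: "Mean change from baseline will be assessed for each of these outcomes for active intervention and control groups".
- Secondary analyses under {20a}: a mixed MANOVA with intervention versus waitlist as the between-group factor and "repeated measures on secondary outcomes (loneliness, expressed anger, work and social adjustment").

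The schedule says otherwise. Of WSAS, Secondary outcome measures states: "This will be measured 2-week pre-intervention and at a 6-month and 12-month follow-up since it will not be sensitive to short-term change". The same section explains that long-term measures cannot be part of the randomised comparison "because the waitlist group will receive the intervention after the RCT 4-week data collection is completed", and that the later surveys will therefore "provide pre- and post-data from the intervention fishing group only at 6 months and 12 months after their intervention". Trial design {8} agrees: "The total follow-up period is 12 months (intervention group only").

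**The concern.** A between-arm analysis of change needs a baseline and at least one later value in each arm, with the control arm still untreated at the later time. The stated schedule gives WSAS no such time. A secondary objective written as a randomised comparison therefore cannot be answered from the data to be collected.

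If this is left alone, the gap will surface at analysis. Someone will then have to decide what to do without a rule, for example by setting 6-month values in the active arm against baseline values in the controls. That would be an uncontrolled contrast reported under a randomised objective.

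**Working it through.** **Inputs.** The assessment times come from Secondary outcome measures. The restriction on late follow-up comes from the same section and from Trial design {8}. The planned 132 controls come from Recruitment sample size.

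**Assessment times by arm, as stated**

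| Measure | Active arm, after baseline | Waitlist arm, after baseline and before treatment | Times in both arms |
|---|---|---|---|
| Loneliness (SELSA-S) | 2 and 4 weeks; 6 and 12 months | 2 and 4 weeks | 2 and 4 weeks |
| Expressed anger (STAXI) | 4 weeks; 6 and 12 months | 4 weeks | 4 weeks |
| WSAS | 6 and 12 months | none | none |

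The loneliness row rests on "2 weeks prior and 2- and 4-week post-intervention". A baseline WSAS in controls is compatible with the text, but a baseline alone gives no change score.

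**Consequence for WSAS.** The group-by-time effect is

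(active mean after − active mean before) − (control mean after − control mean before).

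The control mean after baseline has 0 of 132 scheduled observations, so the second bracket cannot be computed and the effect cannot be estimated.

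**Consequence for a joint model.** If SELSA-S, STAXI and WSAS are entered together and only cases complete on all three are kept, the number of usable controls is also 0. With WSAS left out, the model has baseline and 4-week values of SELSA-S and STAXI scheduled in both arms and can be run.

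**Does the sample size depend on this?** No. It is built on PCL-5 with d = 0.52, two-sided alpha 0.05 and 95% power. The normal approximation gives 2 × (1.960 + 1.645)² / 0.52² = 96.1, or 97 per arm. The two-sample t-test calculation gives 97.09, or 98 per arm and 196 in total, which matches the stated figure. WSAS does not enter it.

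**The case against.** The strongest reply is that the protocol already contains the workable reading. The abstract names only loneliness and expressed anger as secondary outcomes compared from baseline to 4 weeks. Secondary outcome measures lists social functioning among the measures taken in the intervention group at 6 and 12 months. The secondary analyses already plan a within-participant analysis at those times. On this view WSAS is simply named in the wrong list. That is a fair account of how the conflict probably arose, and it makes the correction easy. It does not remove the conflict, since the objective, the outcome sentence and the MANOVA all still state the comparison.

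A reader might go further and infer that the randomised comparisons of loneliness and anger are lost as well. The documents do not support that. It would require joint entry with complete-case deletion. The section on missing data {20c} plans no imputation but leaves multiple imputation and maximum likelihood open, and defers the detail to a statistical analysis plan. An analyst would also see the empty control cells and drop WSAS. Both other scales are scheduled at 4 weeks in both arms, so no data on them are lost.

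Three other defences do not hold for WSAS itself:

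- Imputation or likelihood methods cannot supply the contrast. With no control observed after baseline, the answer would come wholly from the model's assumptions.
- Following waitlist participants after their own delayed sessions would not help, because by then they are no longer untreated.
- The SPIRIT timeline figure could not be inspected. A 4-week WSAS there would contradict the text, so the passages would still need reconciling.

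**Conclusion.** The point stands for WSAS. As written, its between-arm analysis has no post-baseline control data (0 of 132 planned controls) and cannot be run. This rests on the stated schedule and on the statement, made twice, that follow-up beyond 4 weeks covers the intervention group only. It needs no numerical assumption.

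Severity is moderate. One secondary measure is affected. The PCL-5 analysis, the sample size of 196 and the 4-week comparisons of loneliness and anger are not. The effect on those two scales is conditional on a joint complete-case model, which the protocol does not fix. Nor does this defect show that MANOVA is the wrong method for them: taking WSAS out is enough to make that analysis feasible.

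**What to change.** Reconcile the text in three places:

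1. Objectives {7}: take work and social adjustment out of the between-arm item. The long-term item names only the primary outcome measures, so add WSAS there.
2. Secondary outcome measures: limit the sentence on change in both arms to SELSA-S and STAXI.
3. Secondary analyses: remove work and social adjustment from the mixed MANOVA, leaving SELSA-S and STAXI at baseline versus 4 weeks.

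Report WSAS only in the within-participant 6- and 12-month analysis of the intervention group, and label that result as uncontrolled.

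The cost is wording, plus the approvals that the protocol requires for any change (sponsors, University Ethics Committee, Health Research Authority). No new data are needed.

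Adding WSAS to the 4-week survey is not a good substitute. It runs against the protocol's own reason for not measuring the scale in the short term. Recruitment began in March 2024 and ends in September 2026, and the article appeared in February 2026, so participants already past 4 weeks could not supply the value and coverage would be partial.

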### Interim analyses {21b}

The intervention is brief, consisting of a 2-day/1-night weekend, and follow-up surveys occur within 4 weeks. The trial is subject to a power analysis for a final sample size of 196 with no early stopping and no interim analyses. The intervention is minimal risk due to the nondrug nature of the intervention. Injuries occurring on the intervention are reported, and this does not require an interim analysis.

### Methods for additional analyses (e.g. sub-group analyses) {20b}

In order to check whether the equivalence between the active and control groups was equal before the intervention, we run independent samples *t*-tests or chi-square tests for the service record, health, and sociodemographic characteristics (PTSD score, self-assessed impact of PTSD, physical disabilities, medication, age, ethnicity, relationship status, employment status, annual income, fishing experience, social contact).

### Methods in analysis to handle protocol non-adherence and any statistical methods to handle missing data {20c}

There is no protocol for non-adherence because of the brief nature of the intervention. Analysis will be per-protocol (efficacy) and intention-to-treat (effectiveness). We will evaluate the extent of missing data. We do not plan to impute missing values but may consider multiple imputations or maximum likelihood analyses. A detailed statistical analysis plan will be agreed to before the end of data entry.

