### Strategies to improve adherence to interventions {11c}

The intervention takes place over 2 days/1 night. Attendance logs are taken of active group participants arriving for the intervention. In the week prior to the intervention, participants are contacted by telephone and reminded how to find the venue. They are also given reassurance about what they will have to do during the 2-day intervention. Participants who attend the intervention are also compensated £50 GBP towards their travel expenses. Waitlist control group activities are not monitored.

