### Sample size {14}

#### Power analysis

Our main dependent variable will be PTSD symptoms (as measured using the PCL-5). The results from our developmental phase showed a significant group × time interaction for PCL-5 scores, with significant improvements at 2-week and 4-week post-intervention for the angling but not the control group. Given that the purpose of the NIHR call is to build robust evidence for the clinical impact of NBIs, it is imperative that study power should be based on the main DV of interest with the lowest difference scores (i.e. a difference score that will allow the power calculation of a sample large enough to detect a significant effect (should there be one). This is the effect size observed between groups at 4-week post-intervention in the developmental phase (Cohen’s d = −0.52). For a 2-tailed test with 95% power, an alpha of 0.05, and *d* = −0.52 effect size, the power analysis provides a sample size of *n* = 196 (98 participants in each group).

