#### Recruitment sample size

The attrition rate after randomisation in the development phase was approximately 25%. We aim to randomise our power analysis sample size + 30% for the main phase. Thus, we aim to randomise 196 + 30% = 254.8 participants (rounded to 264: 132 intervention, 132 controls to facilitate 12 participants per intervention). By rounding to 264, we can ensure slots are filled across 22 scheduled sessions of 12 participants each. We have designed an RCT with 11 active intervention groups and 11 waitlist control interventions to be delivered after RCT data are collected. We will run eight angling interventions (four active and four controls) sequentially (a maximum of *n* = 12 participants in each session) in years 1 and 2 and six interventions (three active and three controls) in year 3.

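### With no imputation by default, the primary MANOVA is a complete-case analysis under an intention-to-treat label, and efficacy is tied to a per-protocol contrast that randomisation does not protect

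*Protocol article*

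**What the plan says.** On analysis sets, section {20c} of the protocol article states "Analysis will be per-protocol (efficacy) and intention-to-treat (effectiveness". It defines neither set and does not say which one decides the trial. On missing data the same section states "We do not plan to impute missing values but may consider multiple imputations or maximum likelihood analyses", with no condition that would trigger either option. It leaves the detail to a statistical analysis plan to be agreed before data entry ends.

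The primary outcome analysis in {20a} is a mixed MANOVA with group as the between-participant factor and repeated measures on all outcomes, baseline against 4 weeks. The primary measures are PCL-5, PHQ-9, GAD-7 and the short WEMWBS, collected at baseline, 2 weeks and 4 weeks ({12}).

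Under Recruitment sample size: "The attrition rate after randomisation in the development phase was approximately 25" per cent. The target is 264 randomised (132 per arm), and {21b} speaks of a final sample of 196.

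On adherence, {11c} states "Attendance logs are taken of active group participants arriving for the intervention" and says that what waitlist participants do is not observed. Section {11d} rules out no concomitant care. The secondary outcomes text in {12} places the waitlist group's intervention after their 4-week data are in. The title and abstract frame the trial as a test of efficacy, and {8} calls it a superiority trial.

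**The concern.** A classical repeated-measures MANOVA keeps only participants who have every included measure at every included time point. Without imputation, its result is for completers, whatever the analysis set is called. A participant who answers at 2 weeks and is lost by 4 weeks contributes nothing, although {11b} retains data collected up to withdrawal.

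The second part concerns labels. In a superiority trial, the comparison of everyone as randomised should carry the main claim. Here the word that describes the trial's question, efficacy, is attached to the per-protocol set. Only one arm has anything to adhere to before the endpoint. A per-protocol set based on attendance would therefore compare active-arm attenders with all controls, including controls who would not have attended. Randomisation does not protect that comparison.

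If people who do not attend or do not answer change differently from those who do, and this differs by arm, both results could be shifted. The plan has no rule for which one decides if they disagree.

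**Working it through.** **1. The plan's own figure.** The inputs from Power analysis are "For a 2-tailed test with 95% power, an alpha of 0.05" and d = 0.52. Normal approximation: n per arm = 2(1.960 + 1.645)² / 0.52² = 25.99 / 0.2704 = 96.1, so 97. With the t distribution the solution is 97.09, so 98 per arm and 196 in total, with power 95.2%. This matches "98 participants in each group". Inflation: 196 × 1.30 = 254.8, raised to 264.

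**2. Who enters the MANOVA.** Take attrition of 25% to mean no complete 4-week set.
- Lost: 264 × 0.25 = 66.
- Analysed: 264 − 66 = 198, or 99 per arm.
- The protocol's own final sample gives nearly the same share: 196 / 264 = 74%.
- Power at 99 per arm is 95.4%. At 30% attrition (about 92 per arm) it is 94.0%.

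The sample size is thus set on completers and power is adequate. The issue is possible bias and the loss of randomised participants from the result. The count of 66 would rise if single scales were also missing among people who otherwise responded.

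**3. Where adherence exclusions can fall before 4 weeks.**

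| | Active | Waitlist |
|---|---|---|
| Something to attend | yes | no, offered only after 4-week data |
| Adherence recorded | attendance log | none |
| Care that would breach the protocol | none | none |

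With an assumed non-attendance rate q, an attendance-based set drops 132 × q active participants: about 13 at q = 10% and 33 at q = 25%. It drops no controls. The documents give no value for q.

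**4. Size of a possible bias (assumed inputs).** Let m be the proportion lost or excluded in an arm. Let s be the amount by which those people's change to 4 weeks would have been less favourable than that of those retained, in the SD units of the effect size. The bias in favour of angling is

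bias = m(active) × s(active) − m(control) × s(control).

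For 25% of the active arm with a shift and no shift among controls:

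| s | Bias (SD) | Share of 0.52 |
|---|---|---|
| 0.1 | 0.25 × 0.1 = 0.025 | 5% |
| 0.2 | 0.25 × 0.2 = 0.050 | 10% |
| 0.3 | 0.25 × 0.3 = 0.075 | 14% |
| 0.5 | 0.25 × 0.5 = 0.125 | 24% |

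Other cases:
- Equal loss and equal shift: 0.25s − 0.25s = 0.
- Loss of 30% and 20% with a shift of 0.5 in both arms: 0.15 − 0.10 = 0.05 SD.
- If the larger loss or shift is among controls, the sign reverses.

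For an attendance-based per-protocol set, m(control) = 0, so any shift among non-attenders passes straight into the difference.

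**The case against.** The strongest reply is that {20c} keeps multiple imputation and maximum likelihood open and defers to a statistical analysis plan that is not shown. Defining analysis sets and sensitivity analyses is usual content for that plan, so their absence here is no fault. This stands: a reader should not infer that imputation or likelihood methods have been ruled out. What remains is what the protocol does state, namely a listwise model, a default of no imputation without a trigger for departing from it, and efficacy assigned to per-protocol.

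Four stronger readings are tempting, and the document does not support them.

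- *Per-protocol can remove only active participants.* The set is undefined. Ineligibility or missed surveys could remove controls too. The one-sided statement holds only for exclusions based on adherence.
- *Per-protocol decides the primary claim.* Section {12} introduces the primary outcomes with the word effectiveness, which {20c} ties to intention-to-treat. The article uses both words, so the labels are ambiguous rather than decisive.
- *Type I error rises to about 14%.* That figure takes a bias of 0.125 SD, 99 per arm and the standard error of a single-time comparison, √(2/99) = 0.142. With no controls removed (99 against 132) the same reasoning gives about 15.6%. Either way, it uses the 25% attrition as a non-attendance rate, whereas the Discussion links that attrition to difficulty in completing follow-up surveys. The planned test is also of change, in which a stable difference in severity between attenders and non-attenders cancels.
- *The bias favours angling.* The Discussion says the population is hard to engage. It does not say that loss differs by arm or that those lost do worse.

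It is also fair that the protocol allows for attrition in its numbers: 198 expected completers exceed 196.

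**Conclusion.** The point holds in limited form. As written, the default primary analysis is a complete-case analysis, and at the protocol's own expected attrition about 66 of 264 randomised participants are missing from the result called intention-to-treat. Neither analysis set is named as primary. The label efficacy goes to the set in which adherence-based exclusions can fall only on the active arm.

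The count of 66 rests on the development-phase rate of about 25%, for which no split by arm is given. The size and direction of any bias cannot be derived from the document. Bias requires loss or non-attendance that is related to change in symptoms and differs by arm. The range of 0.025 to 0.125 SD is an illustration under assumed shifts, and zero is also possible. Power is not the problem, and recruiting more participants would not remove such a bias.

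**What to change.** - State that the analysis of all randomised participants, as allocated, is primary and carries the efficacy claim.
- Turn the maximum-likelihood option from a possibility into a commitment: a repeated-measures model of PCL-5 at baseline, 2 and 4 weeks, with the 4-week group difference read from it. Participants with 2-week but no 4-week data then contribute.
- Because that model assumes data are missing at random, add a pre-specified sensitivity analysis for data not missing at random, for example with delta-adjusted imputation.
- Define the per-protocol set for both arms and label it supportive. A complier-average causal effect using the attendance log is an optional alternative for the effect among attenders. It assumes that allocation has no effect on non-attenders, which the telephone contact before the session could weaken.

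The cost is changed wording in the protocol and analysis plan and some extra programming. No new data are needed, and recruitment is stated to run to September 2026, so the change can be made before the analysis.
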